
#### Time needed to treat (TNT)

With respect to implementation, we will also estimate the TNT for the interventions. The TNT is a new method designed to consider clinician’s time as a finite resource, with the aim of facilitating for guideline committees who develop clinical practice guidelines. The TNT can be expressed in three different ways: (I) the clinician time needed to improve the outcome for one person (TNT_NNT_), (II) the clinician time needed to provide the intervention for all eligible in a population (absolute TNT), and (III) the proportion of the total clinician time available for patient care needed to implement the intervention for everyone eligible (relative TNT). More detailed information on the TNT method and its assumptions is available elsewhere [46].

### Unintended side effects

Unintended side effects of the interventions experienced by study participants will be assessed through self-report at baseline and at 6 months and 12 months post intervention. Participants will be asked to rate their degree of perceived stress during the past 12 months on a scale from 0 to 50, ranging from “no stress” to “very high level of stress.” They will also respond to a question which reads “Have you experienced any negative consequences as a result of your participation in the trial?”, with two fixed response categories (“yes” or “no”). Those responding “yes” will then be asked to provide an open answer, specifying the negative consequences. Additionally, the collection of data on the target outcomes (CVD and T2D incidence) through extended observational follow-up will provide additional evidence regarding whether any short-term benefits in surrogate markers translate into reduced risk of the target outcomes, of importance from a risk–benefit balance discussion.

### Statistical analysis

Baseline characteristics in the two arms will be described by means of typical summary measures e.g., means, medians, frequencies, proportions, standard deviations, quartiles, and counts. Characteristics of dropouts will be explored in comparison to non-dropouts.

The core tool of outcome analysis will be a hierarchical model consisting of two levels, individuals and PCCs. The primary model for analyzing changes in systolic blood pressure (primary outcome), other biological risk factors, lifestyle habits, and HRQoL over 6 and 12 months will be a mixed-effects generalized linear model (GLM) to capture variability between and within PCCs. Following the GLM framework, the assumptions concerning the underlying probability distribution and the link function (the way the expected value of the outcome is related to a set of independent variables and their associated effects) will differ between continuous, binary, categorical, and count outcomes. In these models, the treatment effect (HDI versus OS) will be assessed using a fixed effect represented by a dummy variable at PCC level, specifying the type of treatment (HDI/OS). Together, this enables the estimation of the average treatment effect, while accounting for the hierarchical structure of the data. We will estimate unadjusted effects and effects adjusted both/either at the individual level and PCC level, e.g., adjusted for demographic characteristics, socioeconomic status, CNI level, and baseline values of the referred outcome. The analyses will be conducted on an intention-to-treat basis and will be carried out using the *glmer* function of the *lme4* package under the R platform [47]. Potential effect modification will be explored through subgroup analyses and interaction analyses considering sex, birth country, and socioeconomic characteristics. A sensitivity analysis will be conducted to assess whether the individual randomization of a single PCC introduced bias. Thus, we will perform analyzes both including and excluding this PCC. The occurrence of missing data will be dealt with accordingly.

For the assessment of T2D and CVD incidence and mortality during the extended 5 and 10 years of follow-up, we will calculate hazard ratios using a mixed-effect Cox regression model and packages *survival* and *coxme* under the R platform [48–50]. We will also calculate the number needed to treat (NNT).

#### Health economic evaluation

For the short-term health economic evaluation, a healthcare costing perspective will be used, including utilization of healthcare in primary, specialized outpatient, and inpatient care as well as medication. Data from the VAL database will be used for this analysis. Total health resource use and associated costs in each arm will be accumulated and analyzed over the 12-month follow-up. Net costs, which is the difference between intervention costs and total health resource use of participants, will thereafter be estimated for both arms. Total QALYs at 6 and 12 months in each arm will be calculated by using the area under the curve method [51]. Incremental differences in QALYs and costs between participants in the HDI and OS arm at 6 and 12 months will be assessed using GLM models with gamma distribution for cost outcomes and gaussian for QALYs. Logistic regression analyses will be used for estimating between-group differences in persons with blood pressure target attained. Between-group differences in healthcare costs will be analyzed while controlling for baseline costs, while baseline utilities will be controlled for in analyses of accumulated QALYs between groups. The cost per QALY and per blood pressure target attained will be assessed using the incremental differences between the groups at 12 months.

For the long-term assessment of cost-effectiveness, total healthcare resource use and its associated costs will be accumulated and analyzed over the 5- and 10-year follow-up period, employing the same data source (VAL) and analytical framework (GLM) as for the short-term assessment. Intervention costs will also be used in this evaluation for the estimation of net costs. Incident cases of T2D and CVD will similarly be accumulated over the follow-up period, and incremental differences at 5 and 10 years will be assessed using logistical analyses. The total costs and health outcomes will be analyzed in a cost-consequence analysis. Furthermore, accumulated deaths due to T2D and CVD over the 5- and 10-years follow-up will be used to assess incremental life years gained between the two groups, and this outcome measure will consecutively be used in a cost-effectiveness analysis estimating the cost per life years gained. Probabilistic sensitivity analyses will be employed throughout the short- and long-term analyses to account for parameter uncertainty.

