### Recruitment of participants, eligibility criteria, and informed consent

Patients aged 50–59 years old who are enlisted at the participating PCCs will be considered eligible for invitation to participate in the trial. Each of the PCCs will be asked to invite and enroll patients until they have reached *n* = 100 participants. For PCCs randomized to HDI, a healthcare professional (registered nurse or general practitioner) from the PCC will send a letter by mail to eligible patients, providing brief information about the intervention and a scheduled date and time for a phone call. During the phone call, the healthcare professional will provide more information about the intervention and the potential participant will have the opportunity to ask questions. Previous research indicates that this approach (information by ordinary mail followed by a phone call) could increase attendance rates compared to a mail-only invitation [26, 27]. If the patient expresses an interest in participating, an appointment for the screening and the health dialogue will be scheduled. Based on all enlisted patients, the healthcare professional will invite patients consecutively based on alphabetical order of their surnames. Patients choosing to participate will provide written informed consent and have the possibility to withdraw their participation at any time without the need to state a reason (Additional file 2). As part of the participant information and informed consent, participants are made aware that the trial is designed to evaluate how well HDI and OS can detect biological risk factors (surrogate endpoints) for T2D and CVD (target outcomes) and whether they lead to reduced risk of T2D and CVD in the long-term.

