For PCCs randomized to OS, eligible patients will be identified upon scheduling an appointment at their PCC for any reason, except for those whose scheduled appointments are related to hypertension, T2D, and CVD, or acute events requiring immediate care or immediate referral. Upon scheduling the appointment, the healthcare professional (assistant nurse, registered nurse, or general practitioner) will provide brief information about the trial. Next, once the patient arrives for their visit, they will again be given information about the trial. If agreeing to participate, they will provide written informed consent and have the possibility to withdraw their participation at any time without the need to state a reason (Additional file 3). Figure 2 shows the timeline of the study, including timepoints for enrollment, allocation, and assessments, as per SPIRIT guidance.

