#### Opportunistic screening (OS)

Patients consenting to participate in the trial, and enlisted at a PCC randomized to OS, will receive an intervention including screening for a smaller set of selected risk factors. The intervention will be conducted as follows. In conjunction with the participant’s scheduled appointment at the PCC, a screening is conducted by the healthcare professional with whom the patient has the appointment. The screening includes measurement of blood pressure, body weight, and height, and the patient is asked about tobacco usage. In total, the appointment is scheduled to take about 15 min. Thereafter, the patient is instructed to provide blood samples within 7 days, where cholesterol levels and glucose levels will be measured. Detected risk factors for T2D and CVD will be managed according to the existing care programs and clinical practice guidelines (https://viss.nu/), which should always include lifestyle advice as the first intervention. However, unlike the HDI, participants will not be offered an individually oriented health dialogue. There are no criteria for discontinuing the intervention and there is no concomitant care that is prohibited during the trial. Figure 3 presents a visual illustration of the core components of HDI and OS.

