### Process and implementation outcomes

Process and implementation outcomes will be assessed 6 months post intervention according to Proctor et al.’s taxonomy [41]. Adoption will be measured as the number of invited PCCs that agree to participate in the study. Healthcare professionals’ perceptions of how acceptable, appropriate, and feasible the interventions are to implement within the context of the PCCs will be assessed using the Acceptability of Intervention Measure, the Intervention Appropriateness Measure, and the Feasibility of Intervention Measure [42]. The measures consist of four items each and responses are reported on a 5-point Likert scale ranging from “completely disagree” to “completely agree.” Fidelity will be operationalized as adherence to the original intervention protocols and assessed using data from electronic medical records. For the HDI, we will report to what extent (proportion) all parameters of the screening have been assessed and whether the following health dialogue has been conducted, as based on documentation in the patients’ electronic medical records. For the OS, we will assess to what extent (proportion) all parameters of the screening have been assessed and to what extent that identification of an elevated risk factor has resulted in measures taken according to existing clinical practice guidelines. (For example, what proportion of participants who report daily smoking are given brief advice about smoking cessation and asked whether they want a referral to a qualified tobacco cessation advisor.) Penetration will be assessed in terms of the proportion (in both arms) of patients choosing to participate among those invited (attendance rate), and the reasons for declining participation among non-participants. We will also report (in both arms) the representativeness of participants as compared to the total eligible population based on socioeconomic characteristics. Participants data on sex, level of education, occupation, annual income, and birth country will be compared to that of the total eligible population, using data from the Longitudinal Integration Database for Health Insurance and Labour Market Studies (LISA) [43]. LISA is managed by Statistics Sweden (the agency of government statistics), which has a 100% coverage for all Swedish citizens aged > 16 years since 1990 and for all aged > 15 years since 2010. In Stockholm Region, the data from LISA is already integrated with the VAL database and used routinely. Additionally, we will assess case-finding rates (in both arms) defined as the proportion of participants where elevated levels of T2D and CVD risk factors are detected for the first time, e.g., the proportion of participants with prediabetes defined as a fasting blood glucose of 6.1–6.9 mmol/l and hypertension defined as blood pressure of ≥ 140/90 mmHg. Finally, semi-structured interviews will be conducted with one healthcare professional and potentially one manager from each participating PCC, with the aim of exploring barriers to and facilitators for implementation of the interventions. The interviews will be audio-recorded, transcribed verbatim, and analyzed using deductive content analysis [44]. The Consolidated Framework for Implementation Research will be used to guide the analysis [45]. Costs related to implementing and running HDI and OS will be analyzed using a bottoms-up, micro-costing approach. This includes staff training, time spent delivering the interventions, necessary materials, IT-infrastructure, etc.

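### The cost and QALY comparison starts the clock at different kinds of contact in the two arms, and neither the cost rule nor the baseline adjustments separate that contact from the arm effect

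*Protocol article*

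**What the plan says.** **Entry.** The recruitment section of the protocol article says that in OS "eligible patients will be identified upon scheduling an appointment at their PCC for any reason". Appointments for hypertension, T2D or CVD are excepted, as are "acute events requiring immediate care or immediate referral". The OS section adds that "a screening is conducted by the healthcare professional with whom the patient has the appointment". In HDI, "the healthcare professional will invite patients consecutively based on alphabetical order of their surnames", working from all enlisted patients. For those interested, "an appointment for the screening and the health dialogue will be scheduled".

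**Costs.** Under Health economic evaluation, the scope is primary, specialized outpatient and inpatient care plus medication, taken from VAL: "Total health resource use and associated costs in each arm will be accumulated and analyzed over the 12-month follow-up". The comparison controls for baseline costs; the look-back window is not given. Intervention cost is a separate component. Under Process and implementation outcomes: "Costs related to implementing and running HDI and OS will be analyzed using a bottoms-up, micro-costing approach", and this includes staff time for delivery.

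**QALYs.** EQ-5D is collected at baseline, 6 and 12 months. QALYs are the area under the curve, and "baseline utilities will be controlled for in analyses of accumulated QALYs between groups". The 12-month differences feed the cost per QALY.

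**The concern.** In OS, time zero coincides with care the patient was already seeking. In HDI it coincides with a contact that exists only because of the programme. A total-cost rule that runs from entry makes no distinction between the two.

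Three consequences follow:

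- OS can be charged with a visit, and any resulting tests, revisits or prescriptions, that screening did not cause.
- The enrolment contact is primary care, so it can appear in VAL while its delivery time is also micro-costed.
- A utility measured around a care visit may not represent the same underlying state as one measured ahead of a planned preventive visit, which weakens baseline utility as an adjustment variable.

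Aims II (HRQoL), V (resource use) and VI (cost per QALY) are exposed. The Discussion says the results may underpin decisions on scaling up the programme.

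**Working it through.** The protocol states no cost or QALY figure to reproduce. The check asks what the specified estimators return when the true arm effect is zero. Differences are OS minus HDI throughout.

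**QALYs**

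Inputs from the plan: EQ-5D at 0, 6 and 12 months, area under the curve, Gaussian model adjusted for baseline utility. Assumed, because the documents give none: a dip d in OS utility at baseline, a share r of it recovered by 6 months and unchanged to 12, and a within-arm slope rho of follow-up on baseline utility.

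1. AUC = 0.25*u0 + 0.5*u6 + 0.25*u12.
2. Unadjusted difference = -0.25d - 0.75d(1 - r).
3. Within-arm slope of AUC on u0 = 0.25 + 0.75*rho. The baseline difference is -d, so adjustment adds (0.25 + 0.75*rho)d.
4. Adjusted difference = 0.75*d*(rho - 1 + r).

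A positive value counts against HDI. It is positive only when r exceeds 1 - rho.

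| r | d = 0.05, rho = 0.6 | d 0.02 to 0.08, rho 0.5 to 0.7 |
|---|---|---|
| 1 | 0.75 × 0.05 × 0.6 = +0.0225 | +0.0075 to +0.042 |
| 0.5 | 0.75 × 0.05 × 0.1 = +0.004 | 0 to +0.012 |
| 0.4 | 0 | depends on rho |
| 0 | 0.75 × 0.05 × (-0.4) = -0.015 | -0.030 to -0.0045 |

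A null simulation of 400,000 people agrees. It assumed a between-person SD of 0.12 and a within-person SD of 0.08, so rho = 0.0144/0.0208 = 0.69. At d = 0.05 it gave adjusted differences of +0.026, +0.007 and -0.011 for r = 1, 0.5 and 0. At r = 1 the unadjusted difference was -0.012, so in that case adjustment reversed the bias and enlarged it.

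**Costs**

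Assumed: OS carries extra episode cost E, a share s of which falls after entry and the rest in the baseline window; the slope of follow-up on baseline cost is b. In a linear model (the plan uses a gamma model, so this is an approximation):

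adjusted difference = sE - b(1 - s)E.

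With b = 0.5:

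- s = 1 gives +E. Adjustment removes nothing.
- s = 0.5 gives 0.5E - 0.25E = +0.25E.
- s = 0 gives -0.5E, which makes OS look cheaper.

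Simulation with E = 3000 (arbitrary units) gave +3158, +589 and -1480. The sign turns on s, which depends on a baseline window the article does not define.

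**Enrolment contact**

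The HDI appointment is scheduled at 75-90 minutes and the OS one at about 15. If each contact stays in VAL and is also micro-costed, the duplicated contact is longer in HDI by 60 to 75 minutes (75 - 15 and 90 - 15). The booked OS visit itself has no HDI counterpart. The two distortions can pull in opposite directions.

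**The case against.** **The exclusions shrink the problem.** Urgent acute events and visits for hypertension, T2D or CVD are removed, and an appointment for any other reason includes routine ones. This stands: many OS participants may have no sharp dip and little follow-on care.

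**The timing of the OS EQ-5D is not stated.** The OS visit is described as blood pressure, weight, height and a tobacco question; EQ-5D is not listed. This also stands, and the QALY part is conditional on it.

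**Contact coding and the baseline window are details for a fuller plan.** That is partly right. If the full plan already removes the enrolment contact, that part is met. But the article does fix total all-cause cost over 12 months and the two baseline adjustments, and applied as written these do not isolate the contact.

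**The Discussion already concedes selection bias from recruitment after randomization, in an unpredictable direction, and plans covariate adjustment.** The concession is fair. It does not address different entry events, and covariate adjustment is what can fail when a transient state is measured at entry in one arm only.

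A reader might go further and infer that costs are biased in favour of HDI, QALYs against it, and the cost per QALY wrong in sign. The documents do not support that. The QALY direction needs r above 1 - rho. The cost direction needs most episode cost to fall after entry. Clinic attenders with lasting ill health would have low r.

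**Conclusion.** The point holds as a problem of how the cost rule and baseline adjustments are specified. The arms enter at different kinds of contact, the 12-month cost rule does not separate that contact, and the stated adjustments cannot be relied on to do so. OS costs can include care OS did not cause, and the enrolment contact can be counted in two components; double counting is possible, not established.

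The QALY bias is conditional on the OS baseline EQ-5D being taken around the care visit. Over the assumed ranges it lies between -0.030 and +0.042 (OS minus HDI) and is zero at r = 1 - rho. The cost bias runs from about +E to -0.5E at b = 0.5. None of d, rho, r, E, s or b is in the documents, so neither size nor direction can be claimed. The change is worth making because it is cheap and the estimates feed the cost per QALY.

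**What to change.** In the Health economic evaluation section:

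1. Exclude the enrolment-day contact from VAL costs in both arms, and count intervention delivery only through micro-costing.
2. End the baseline-cost window before the OS appointment is booked and before the HDI invitation is sent, so that episode cost cannot enter the adjustment variable.
3. Add a sensitivity analysis that starts cost accumulation at day 90 in both arms. Day 90 is a convention to be fixed in advance.
4. Beside the baseline-adjusted QALY model, report months 6-12 QALYs adjusted for register covariates (age, sex, socioeconomic status, prior-year care and drugs), as a sensitivity analysis only. It avoids the baseline dip, but if the covariates absorb nothing it carries its own bias of -0.5d(1 - r), so it should not replace the main model.

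Two steps are best avoided. Removing index-complaint care from OS alone would leave incidental episodes in HDI and create a new asymmetry. Making a QALY claim conditional on both models agreeing would turn a sensitivity analysis into a gate.

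The cost is plan wording and some programming on data already due to be collected. Precision falls slightly, and early effects are left out of the sensitivity analyses.

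### Net cost is defined in each arm as the difference between intervention cost and healthcare use, but both are payer costs and an arm's cost is their sum

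*Protocol article*

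**What the plan says.** All but one of the statements are in the protocol article under Health economic evaluation.

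- The costing perspective is that of the healthcare system, "including utilization of healthcare in primary, specialized outpatient, and inpatient care as well as medication".
- Healthcare use is taken as a total within each arm: "Total health resource use and associated costs in each arm will be accumulated and analyzed over the 12-month follow-up".
- Net cost is then defined: "Net costs, which is the difference between intervention costs and total health resource use of participants, will thereafter be estimated for both arms".
- Between-arm differences are estimated "using GLM models with gamma distribution for cost outcomes and gaussian for QALYs".
- The short-term ratios follow: "The cost per QALY and per blood pressure target attained will be assessed using the incremental differences between the groups at 12 months".
- The 5- and 10-year evaluation uses the same construct: "Intervention costs will also be used in this evaluation for the estimation of net costs".

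The intervention cost itself is described under Process and implementation outcomes: "Costs related to implementing and running HDI and OS will be analyzed using a bottoms-up, micro-costing approach". It covers training, delivery time, materials and IT.

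Nowhere does the article say that the two components are added, or that the subtracted term means a saving relative to the other arm.

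**The concern.** Subtracting healthcare from intervention cost is legitimate in one setting: when the subtracted term is the reduction in healthcare use that the intervention brings about, taken once, between arms. The article instead subtracts total healthcare use, and does so separately in each arm. The result is neither the arm's cost nor a net saving.

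Cost-effectiveness is part of the overall aim. Specific aims V to VII concern resource use and costs, cost per QALY and per blood pressure target attained, and cost per life year gained. The Discussion says the results may underpin political decisions on scale-up. If the definition is carried literally into the ratios, an intervention that saves healthcare could look more expensive than it is, or the cost of delivering it could be booked as a credit.

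**Working it through.** The article states no cost figure, so there is nothing of its own to reproduce. The check is algebraic, followed by an illustration on assumed costs.

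**Algebra.** Let I be intervention cost and H healthcare and medication cost per participant, with 1 = HDI and 0 = OS, dI = I1 - I0 and dH = H1 - H0.

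- Sum: (I1 + H1) - (I0 + H0) = dI + dH.
- Difference in the order written: (I1 - H1) - (I0 - H0) = dI - dH. Departure from the sum: -2 x dH.
- Difference reversed: (H1 - I1) - (H0 - I0) = dH - dI. Departure from the sum: -2 x dI.
- Healthcare cost alone, if net cost is not used in the ratio: dH. Departure from the sum: -dI.

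The written order agrees with the sum only when dH = 0, and the reversed order only when dI = 0.

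**Illustration.** All costs are assumptions in arbitrary units per participant, with H0 = 20000.

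| I1 | I0 | H1 | dI | dH | Sum | I - H | H - I |
|---|---|---|---|---|---|---|---|
| 1500 | 400 | 18000 | 1100 | -2000 | -900 | 3100 | -3100 |
| 1500 | 400 | 20000 | 1100 | 0 | 1100 | 1100 | -1100 |
| 1500 | 400 | 22000 | 1100 | 2000 | 3100 | -900 | 900 |
| 3000 | 500 | 18000 | 2500 | -2000 | 500 | 4500 | -4500 |
| 3000 | 500 | 20000 | 2500 | 0 | 2500 | 2500 | -2500 |
| 3000 | 500 | 22000 | 2500 | 2000 | 4500 | 500 | -500 |

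First row: (1500 + 18000) - (400 + 20000) = -900, so HDI saves money. In the written order, (1500 - 18000) - (400 - 20000) = -16500 + 19600 = 3100. With an assumed gain of 0.01 QALY, the ratio is -900 / 0.01 = -90000 on the sum and 3100 / 0.01 = 310000 on the written definition. The third row shows the opposite: extra healthcare use turns a true cost of 3100 into an apparent saving of 900.

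**Fit with the stated model.** A gamma distribution needs positive values. I simulated H as gamma with mean 20000 (assumed) and took the share of participants with I - H at or below zero:

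| CV of H (assumed) | I = 1500 | I = 400 |
|---|---|---|
| 1 | 92.7% | 98.0% |
| 2 | 59.4% | 70.8% |
| 3 | 38.0% | 46.5% |

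For H - I the shares are the complements: 7.3%, 40.6% and 62.0% for I = 1500, and 2.0%, 29.2% and 53.5% for I = 400. In every scenario some values fall outside what a gamma model can take, whichever way the subtraction runs. The share itself depends entirely on the assumed inputs.

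**The case against.** The best reply is that this is loose wording and that the analysts will model an ordinary total cost. There is support for that. The gamma model suits a positive total, and the long-term paragraph speaks of total costs in the cost-consequence analysis. The article also never says outright that net cost is the ratio numerator: after the definition it refers to costs, then to healthcare costs adjusted for baseline, then to incremental differences. This stands as a limit on the point: the effect on the results is conditional on the definition being followed.

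It does not remove the point. Net cost is the only route by which the section brings intervention cost into the evaluation. If net cost is the numerator, it is wrongly built. If it is not, the ratios as described omit the cost of the intervention being evaluated. The gamma choice is a reason to think a sum was meant, and so a reason to write it.

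Three stronger readings are tempting but not supported. A reader might infer that healthcare savings will necessarily carry the wrong sign in the results; the word used for the subtraction does not fix its order, and in the reverse order it is the intervention cost that is wrong. A reader might infer that net cost is negative for most participants; no cost per participant is given, and on assumed inputs the share for I - H runs from 38% to 98%. A reader might also quote a fixed multiple for the error; it follows only from whichever costs are assumed, and in the written order it vanishes when the arms use equal care.

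**Conclusion.** The definition is wrong as written. Neither order of subtraction yields the payer's incremental cost, dI + dH, and nothing else in the article corrects it. In the written order the error is 2 x dH in size; reversed, it is 2 x dI; with intervention cost left out, it is dI. The conclusion rests on the stated healthcare perspective, under which both components are costs to the same payer. Its effect on the ratios rests on the definition being applied literally, which the text implies without stating. The actual magnitude cannot be given, because the documents contain no costs.

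This is a should-fix matter for the economic aims (V to VII) only. The primary analysis of systolic blood pressure, the randomization and the sample size are unaffected.

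**What to change.** Replace the net-cost sentence with a definition along these lines:

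- Total cost per participant = micro-costed intervention cost + healthcare and medication cost.
- Net (incremental) cost = HDI minus OS of that total.
- This quantity is the numerator of the cost-effectiveness ratios at 12 months, 5 years and 10 years, and total cost is the outcome of the gamma model.

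The same definition should say that intervention contacts are counted once. The regional database covers primary care contacts and the micro-costing covers delivery time, so adding the two without such a rule could count the same visit twice. This belongs to the corrected definition and is not a separate fault of the plan.

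The cost is a sentence or two in the economic section. Both components are already planned for collection, so no new data are needed. Making the change before cost results are seen also avoids a later choice of sign.
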